### Outcomes

#### Primary endpoint

The primary endpoint of the trial is PFS at 12 months, reported as the percentage of participants alive and progression-free at 12 months. PFS is calculated from date of registration to first documented evidence of disease progression or death. Participants who have not progressed at the time of analysis will be censored at the last date alive and progression-free.

#### Secondary endpoints

Safety: Serious adverse events (SAEs) from registration until 30 days post cessation of trial therapy (Selumetinib or I-131 therapy); suspected unexpected serious adverse reactions (SUSARs) and serious adverse reaction (SARs) recorded for all from start of protocol treatment for the lifetime of the trial;Toxicity: Adverse reactions (ARs) as graded by common terminology criteria for adverse events (CTCAE) v4.0;Overall survival (OS): calculated from date of registration to date of death; censoring will occur at last known date alive for those alive at time of analysis;Sufficient iodine uptake: reviewed centrally; sufficient uptake is defined as presence of any clinically relevant uptake in a lesion in which there was previously no uptake or an increase of 30% or more in uptake in a lesion with evidence of some uptake on the baseline scan;Radiological response: assessed via CT scans and based on response evaluation criteria in solid tumours (RECIST) v1.1.

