## Methods

### Design

SEL-I-METRY is a UK, single arm, multi-centre, two-stage phase II proof of concept trial investigating the use of Selumetinib to resensitise iodine refractory patients with differentiated thyroid cancer. To ensure at least 38 participants are treated with I-131, approximately 60 participants will be recruited from eight NHS Hospitals. Participants will receive 75 mg of Selumetinib orally twice daily for four weeks (dose may be reduced due to adverse events) and will then be assessed for evidence of an increase in radioiodine uptake via iodine-123 (I-123) single photon emission computed tomography/computed tomography (SPECT/CT); those showing sufficient uptake will then receive I-131 therapy (further details on patient imaging and dosimetry can be found in Additional file 1). A previous pilot study [21] used I-124 sodium iodide (NaI) although there is currently no commercially available source of this isotope in the UK. This trial therefore elected to use I-123 as an alternative to determine changes in radioiodine uptake following Selumetinib therapy, and to predict likely lesional absorbed dose in participants proceeding to I-131 therapy. The use of I-123 as opposed to I-124 is not thought to pose any significant risk to the current trial; whilst theoretically there may be advantages to using I-124, there are no known clinical comparator studies between the two techniques and a pragmatic decision to use I-123 was deemed reasonable by the trial team. An early stopping rule is incorporated in the case where none of the first 10 patients treated with Selumetinib show sufficient iodine uptake to progress to I-131 therapy; should this happen the trial may be discontinued. The study protocol and this manuscript have been written in accordance with Standard Protocol Items: Recommendations for Interventional Trials (SPIRIT) guidelines [26] (checklist included as an Additional file 2).

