### Secondary objectives

Assess the safety and toxicity of Selumetinib;Assess efficacy based on response and overall survival of Selumetinib followed by I-131 therapy;Determine the rate of iodine uptake in metastatic lesions in iodine refractory patients with differentiated thyroid cancer treated with Selumetinib.

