**Fig. 1 Fig1:**
[figure not shown]
Participant pathway

**Table 2 Tab2:** Minimum schedule of assessments (SPIRIT diagram)

	Baseline		Treatment				End of Treatment	Follow Up
	Within 14 days prior to registration	Within 28 days of registration	Selumetinib			I-131 Therapy	30 days post end of Selumetinib treatment	3 monthly for first 12 months then 6 monthly for duration of trial^b^
			Day 1	Day 14	Day 28			
Informed consent	X							
Patient details (initials, date of birth, sex)	X							
Medical History	X							
Physical Examination/Vital signs	X		X	X	X		X	X
Ophthalmologic assessment	X							
12-Lead ECG	X		X				X	
Laboratory tests	X		X	X	X		X	X
Pregnancy test	X		X			X	X	X^c^
Echocardiography /MUGA	X		X					
Dispensing of Selumetinib			X					
Tissue collection		X						
CT neck, thorax, abdomen and pelvis	X^a^							X
I-123 SPECT/CT		X			X			
SPECT/CT for Lesion Dosimetry post I-131 therapy						X		
Adverse Events	X		X	X	X	X	X	X^d^
Concomitant Medications	X		X	X	X		X	
Quality of life (QLQ-C30, QLQ-H&N35 and EQ-5D™)		X					X	X^e^
Protein bound iodine blood sample collection						X^f^		
Cell-free DNA blood sample collection			X	X	X		X	X^g^

^a^if CT scans have not been performed within 28 days of starting treatment, an additional CT neck, chest, abdomen, and pelvis must be performed to enable assessment of response and progression-free survival as per RECIST criteria

^b^Participants who do not proceed to radioiodine therapy will be followed up for safety purposes until 30 days after completion of Selumetinib treatment only

^c^Pregnancy test to be done at the first and second 3 monthly follow up visits (3 month and 6 month follow-up)

^d^Adverse reactions only at follow up visits

^e^Quality of life is assessed at baseline, end of treatment and 3 monthly for the first 12 months of follow-up

^f^Collected 24 and 144 h following I-131 dosing

^g^3 and 6 months only

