#### Secondary endpoint analyses

SAEs, SARs and SUSARs will be reported overall and by treatment period (Selumetinib, I-131) for all participants and for the IU and non-IU cohorts.

The number and proportion of participants experiencing each grade of toxicity will be summarised in the same analysis sets.

OS will be summarised using Kaplan-Meier curves; OS at 12 months and median OS will both be presented alongside CIs.

The proportion of participants with sufficient iodine uptake to progress to I-131 will be presented with corresponding 95% CI. This will also be presented excluding individuals who did not receive Selumetinib for seven days prior to the scan.

The proportion of participants in the IU cohort achieving at least a partial response will be presented with 95% CIs. The proportion of participants in each best response category (complete response, partial response, stable disease, and progressive disease) will also be presented.

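### Graded toxicity is defined as adverse reactions only, although all adverse events are collected on treatment, so non-serious events judged unrelated have no named summary

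*Protocol article*

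**What the plan says.** Under Secondary objectives, the protocol article sets out to "Assess the safety and toxicity of Selumetinib". Secondary endpoints splits this into two parts:

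- **Safety** covers serious adverse events whatever their cause, from registration to 30 days after trial therapy stops. Serious adverse reactions and unexpected ones (SARs, SUSARs) are followed for the life of the trial.
- **Toxicity** is given as "Toxicity: Adverse reactions (ARs) as graded by common terminology criteria for adverse events (CTCAE) v4.0".

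Secondary endpoint analyses follows the same split. For serious events, "SAEs, SARs and SUSARs will be reported overall and by treatment period (Selumetinib, I-131) for all participants", and also for the two uptake cohorts. For graded toxicity, "The number and proportion of participants experiencing each grade of toxicity will be summarised in the same analysis sets". No summary of non-serious adverse events regardless of cause is named.

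Table 2 has a row headed "Adverse Events". It is marked at baseline, on Selumetinib days 1, 14 and 28, at I-131 therapy, 30 days after Selumetinib, and at follow-up. Footnote d qualifies only the last of these: "Adverse reactions only at follow up visits".

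**The concern.** The endpoint uses only part of the adverse-event data that the schedule gathers on treatment. What separates an adverse reaction from an adverse event is a judgement that the treatment caused it. The Design section says "SEL-I-METRY is a UK, single arm, multi-centre, two-stage phase II proof of concept trial", so there is no concurrent control rate against which to check that judgement.

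The judgement is hard for some of the expected effects. The Selumetinib section of the Background lists dyspnoea and tiredness among the commonest side effects, and both are also plausible in patients with progressing metastatic cancer. A non-serious event put down to the disease leaves the graded summary and appears in no other summary that the article names.

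At stake is how far the answer to a stated secondary objective depends on attributions that the trial cannot verify. The definition may also carry into the exploratory analysis relating whole-body and blood absorbed dose to toxicity grade.

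**Working it through.** The article states no toxicity rate, so there is no figure to reproduce. The check compares the sections and then tests what can be said about size.

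**1. Do the two terms differ in this document?** Yes. Footnote d restricts collection to reactions at follow-up, which has meaning only if the earlier visits collect more than reactions. Secondary endpoints also lists serious events separately from serious reactions. Reactions are therefore a subset of events.

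**2. Which events fall outside every named summary?**

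| | Judged related | Judged unrelated |
|---|---|---|
| Serious | Serious-event report and graded toxicity | Serious-event report |
| Non-serious | Graded toxicity | Collected on treatment, no named summary |

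Only the bottom right cell is missing. It is not confined to mild events, because seriousness and CTCAE grade are different scales and a grade 3 event need not be serious.

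**3. What order must the two rates have?** Fix a window and a grade g. Let A be the participants with any adverse event of grade g or higher, and R those with any adverse reaction of grade g or higher. R is contained in A, so R/N ≤ A/N. The two are equal only if everyone in A also has at least one such event judged related. The bound applies to grade g or higher. It does not apply to the share whose worst grade is exactly g, because counting more events can move a participant from one grade to the next.

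**4. How large could the difference be?** The article gives neither event rates nor attribution accuracy, so every rate below is an assumption. N = 60 is the approximate planned recruitment.

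*Related events missed.* Reported rate = true related rate p × share s recognised as related.

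| s | p = 30%: reported rate (participants) | p = 10%: reported rate (participants) |
|---|---|---|
| 1.0 | 30% (18.0) | 10% (6.0) |
| 0.9 | 27% (16.2) | 9% (5.4) |
| 0.7 | 21% (12.6) | 7% (4.2) |
| 0.5 | 15% (9.0) | 5% (3.0) |

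Over this range the understatement runs from nothing to one half.

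*Background events present.* Take a true related rate of 10% and an independent background rate of 10%. The all-cause rate is 1 − (0.90 × 0.90) = 19%.

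- With perfect attribution the endpoint reports 10%. That is 9 points below the all-cause rate, yet correct for the drug.
- If every background event were blamed on the drug, it would report 19% against a true 10%.

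Error relative to drug-caused toxicity can therefore run either way. Only the order of the reactions-only and all-cause rates is certain.

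**5. Which window supports an all-cause summary?** All events are collected up to 30 days after Selumetinib. For participants without sufficient uptake, that is their whole follow-up. Participants given I-131 continue Selumetinib, where applicable, until two days after it, so the window reaches about 2 + 30 = 32 days after I-131. Beyond that only reactions are collected.

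**The case against.** The strongest reply is that the split is deliberate and coherent: safety covers serious events of any cause, and toxicity covers graded effects attributed to treatment. Nothing in Table 2 contradicts that. The all-cause serious-event report, by period and cohort, already shows the unrelated events of most consequence. The analysis plans are separate and not shown, and may well tabulate all adverse events. An all-cause rate also has a fault of its own, since it counts disease events as if they were toxicity.

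Most of this stands. There is no internal contradiction, and the serious-event endpoint narrows the gap to one cell of the table. A further table in the analysis plan would reduce the practical effect, but it would not change the definition that this document gives to a named endpoint.

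Three stronger readings are tempting and are not supported:

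- **That toxicity will be understated.** Attribution error can run in either direction. The article does not define an adverse reaction or say who judges relatedness, and dyspnoea and tiredness are listed effects of the drug, which gives grounds for attributing them to it.
- **That all-cause data will go unreported.** The article does not exclude such a table.
- **That a comparison with the continuous kinase inhibitors would be biased.** The Discussion contrasts the strategies only in general terms and says a randomised trial could be considered. No comparison of toxicity rates across trials is planned.

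**Conclusion.** The point holds in a limited form, as a minor improvement to an endpoint definition. Graded toxicity is restricted to adverse reactions in a single-arm trial that collects all adverse events through 30 days after Selumetinib. Non-serious events judged unrelated, some possibly of grade 3 or higher, are left without a named summary. For any grade threshold over the same window, the reactions-only rate cannot exceed the all-cause rate. It may understate toxicity by an amount that the article does not allow one to estimate.

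This rests on reading an adverse reaction as an event judged related to treatment, which is the usual meaning and the one implied by footnote d. No sample size, power or primary-endpoint figure is affected.

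**What to change.** Add to the toxicity endpoint a summary of each participant's worst CTCAE grade for any adverse event regardless of cause, from first dose to 30 days after the end of Selumetinib, by cohort and treatment period. This is the window in which all events are collected.

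Keep the adverse-reaction summary alongside it over the whole follow-up. Replacing it with a summary that stops at 30 days would lose the later reactions gathered under footnote d.

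The cost is one extra table and no new data collection. The stated rate may look less favourable and will include some events caused by the disease; showing the reaction column beside it lets the reader see how much of the total depends on attribution.

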#### Exploratory endpoints

Lesional and whole body dosimetry: As measured from a minimum of three and maximum of four SPECT/CT scans over six days following Selumetinib and I-131;BRAF, NRAS and TERT gene mutational status and additional relevant genes: from circulating cell-free DNA, iodine refractory tissue samples and historic tissue samples where available;PBI levels from blood samples;Quality of life: assessed using QLQ-C30 plus head and neck cancer supplementary questions (H&N35), and EQ-5D™;Change in serum thyroglobulin levels: assessed via percentage change from baseline at each time point.

### Analysis

Statistical analysis for final and interim analyses are fully detailed in separate analysis plans. The full analysis set will include all registered participants receiving at least one dose of Selumetinib and will be equivalent to the safety analysis set. The iodine uptake (IU) cohort will include participants from the full analysis set who were deemed to have sufficient I-123 uptake following treatment with Selumetinib. All other participants in the full analysis set will be the non-IU cohort. All efficacy endpoint analyses will be conducted on the IU cohort only, unless otherwise specified in the analysis plan. Safety analyses will be conducted on the safety analysis set with data summarised for each study cohort and overall during initial therapy.

#### Primary endpoint analysis

The proportion of participants alive and progression free at 12 months will be presented with corresponding confidence intervals (CI). The primary analysis will test the hypothesis that PFS in the IU cohort is less than or equal to 25%, against an alternative of 44% based on the Nelson-Aalen estimate of the cumulative hazard function at 12 months, following the methodology of Case and Morgan [27].

#### Secondary endpoint analyses

SAEs, SARs and SUSARs will be reported overall and by treatment period (Selumetinib, I-131) for all participants and for the IU and non-IU cohorts.

The number and proportion of participants experiencing each grade of toxicity will be summarised in the same analysis sets.

OS will be summarised using Kaplan-Meier curves; OS at 12 months and median OS will both be presented alongside CIs.

The proportion of participants with sufficient iodine uptake to progress to I-131 will be presented with corresponding 95% CI. This will also be presented excluding individuals who did not receive Selumetinib for seven days prior to the scan.

The proportion of participants in the IU cohort achieving at least a partial response will be presented with 95% CIs. The proportion of participants in each best response category (complete response, partial response, stable disease, and progressive disease) will also be presented.

#### Exploratory endpoint analyses

The absorbed dose to each lesion, whole body and blood measurements will be presented descriptively alongside measures of uncertainty. Regression modelling will be used to investigate association between these doses and outcome as appropriate. Analogous analyses will explore association between lesional absorbed dose, radiological response and overall survival, as will analyses considering whole body and blood absorbed doses and grades of toxicity.

Gene mutational status will be summarised for all available samples. PFS and response will be summarised by gene mutational status.

PBI measurements will be summarised for all participants receiving I-131 with samples available. The relationship between absorbed dose delivered and treatment outcome will be investigated.

Quality of life will be summarised with 95% CIs adjusting for baseline mean scores. The QLQ-C30 and H&N35 will be summarised for each domain. The proportion of participants scoring each category for the five EQ-5D™ domains will be presented.

Mean change in thyroglobulin from baseline at each time point will be presented with corresponding standard error. Mean change will also be presented by maximum RECIST response. A waterfall plot of maximum change per participant will be presented.

### Trial and data monitoring

A Trial Steering Committee will be convened to periodically review safety data; an independent Data Monitoring and Ethics Committee (DMEC) will review safety data to determine patterns and trends of events which would not be apparent on an individual case basis. Following the interim analysis, the DMEC may request that the trial be terminated for lack of activity if there is evidence to suggest that 12 month PFS is no better than 25% based on the Nelson-Aalen estimator.

## Discussion

The SEL-I-METRY trial will investigate a potential treatment to resensitise radioiodine refractory patients with differentiated thyroid cancer. Current treatment options for this group of patients, the multi-targeted kinase inhibitors Sorafenib and Lenvatinib, need to be given continuously and are associated with significant toxicity and hence may be detrimental to quality of life.

Patients who have radioiodine avid disease have better survival outcomes and thus resensitising refractory patients could lead to improvements in progression-free survival without the need for continuous treatment and the associated toxicity. There are already considerable data regarding the tolerability of the Selumetinib regimen, and a pilot trial found an indication of an increase in iodine uptake. Both toxicity and efficacy will be assessed in this larger Phase II multicentre trial.

If the SEL-I-METRY trial demonstrates that Selumetinib followed by further I-131 NaI is a useful treatment strategy for this group of patients, a randomised trial comparing this approach with other treatments, such as the multi-kinase inhibitors, could be considered to help define the optimal treatment for these patients.

In addition, an essential element of this trial is the need to set up, for the first time, a network of UK centres able to perform quantitative high activity I-131 imaging which is essential for dosimetric calculations. This information will be collected to investigate prediction of response to I-131, presenting an unprecedented opportunity to investigate the role of lesional dosimetry in molecular radiotherapy, leading to greater personalisation of therapy, both with I-131 and with other isotope therapies.

## Trial status

At the time of submission, SEL-I-METRY is open to recruitment.

## Abbreviations

AE: Adverse event
AR: Adverse reaction
CI: Confidence intervals
CTCAE: Common terminology criteria for adverse events
EGC: Electrocardiogram
FBC: Full blood count
GBq: Giga Becquerel
Gy: Gray
I-123: Iodine-123
I-124: Iodine-124
I-131: Iodine-131
IU: Iodine uptake
LFT: Liver function test
MAPKinase: Mitogen-activated protein kinase
MUGA: Multiple gated acquisition
NaI: Sodium iodide
NIS: Sodium iodide symporter
OS: Overall survival
PBI: Protein bound iodine
PET: Positron emission tomography
PFS: Progression free survival
RAI: Radioactive iodine
rhTSH: Recombinant human thyroid stimulating hormone
SAE: Serious adverse event
SPECT/CT: Single photon emission computed tomography/computed tomography
SPIRIT: Standard protocol items: recommendations for interventional trials
SUSAR: Suspected unexpected serious adverse reaction
TFT: Thyroid function tests
TSH: Thyroid stimulating hormone
U&Es: Urea and electrolytes
UK: United Kingdom
